### Follow-up visit

Telephone or outpatient appointment within 90 days from the onset of the neurological deficit. During this visit, the patient’s mRS value, recurrence of symptoms, and clinical condition should be evaluated.

### Quality of life (QoL) evaluation and pharmacoeconomic analysis

We have incorporated a quality of life (QoL) evaluation framework into our study to demonstrate our commitment to a holistic approach to patient care and to enhance the understanding of the benefits of accurate diagnosis beyond the immediate clinical outcome. The QoL framework in our study includes both the Modified Rankin Scale (mRS) and the quality-adjusted life years (QALY) metrics (13).

The mRS is known for its direct relevance to stroke outcomes and its ability to measure changes in functional status. Furthermore, it is simple and easy-to-use tool that is widely accepted and validated in stroke research. In the context of pharmacoeconomic analysis in our study, the mRS provides a quantifiable outcome measure that can be related to QALYs and other economic evaluations. QALYs are commonly used in health economics. Our study aims to highlight how an accurate diagnosis can lead to a better patient outcome and potentially lower healthcare costs over time (14, 15).

### Statistic analysis

A minimum of 718 patients is required to demonstrate significant differences between diagnostic approaches. The analysis involves appropriate statistical tests and logistic regression to assess factors influencing clinical diagnosis. It is expected that the total number of enrolled patients will be 3,000 in order to ensure the availability of all established parameters and, particularly, the relevance of the data obtained. The sample size was determined using the proportional data from the pilot project (*p* = 0.34 for the observation group and a desired effect of at least 10%), 5% significance level, and 80% power.

Numerical variables are presented as medians and ranges or interquartile ranges. Categorical variables are presented as absolute and relative frequencies. The association between demographic, clinical, or radiographic variables and the clinical diagnosis (stroke and stroke mimic) is analysed using appropriate statistical tests—Mann–Whitney test, chi-squared test of independence for contingency tables, or other statistical tests, if necessary. Eventually, logistic regression can be used for analysing the effect of multiple factors on the clinical diagnosis.

The diagnostic accuracy of applied diagnostic methods will be evaluated using common measurements, including accuracy, sensitivity, specificity, positive predictive value, and negative predictive value. The characteristics will be reported with their confidence intervals. The significance level is set to 5%, and statistical analyses will be performed using appropriate statistical software (R, STATA) with maximum available data.

The pharmacoeconomic analysis will include a health technology assessment (HTA) to calculate the potential value of innovation at an early stage, analysing not only the QoL of patients but also the costs associated with the treatment of stroke and SM. The calculation of costs is based on the average cost of thrombolysis and its associated treatment, representing the incremental cost (IC). Economic evaluation is organised as a test of dominance of improved results (meaning fewer complications associated with the administration of thrombolysis) and lower costs.

To calculate the overall benefit, the value of the QoL and the specific parameter of the quality-adjusted life years (QALY) set for the Czech Republic will be used.

The results will be reported as expected ICs and effects (E) expressed in quality-adjusted years of life (QALY).

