### Monitored parameters

The following data will be collected and evaluated in Table 1.

**Table 1 tab1:** Following data will be collected and evaluated.

Patient history	
Age Sex Comorbidities Long-term medication	Hypertension, diabetes mellitus, heart disease, arrhythmia, hyperlipidemia, mental disorders, cephalgia, migraine, epilepsy, oncological disease, cognitive deficit antithrombotic medication, hormonal anticonception
Hospitalisation data	
Date and time of stroke/stroke mimics Date of hospital admission Hospitalisation, duration	standard, ICU
Systolic/diastolic blood pressure Laboratory parameters-INR, glycemia, Increase in liver tests, kidney failure, drugs in the blood	
Clinical data	
mRS NIHSS Neurological deficit Type of treatment Multimodal brain CT scan on admission Follow-up NCCT Brain MRI results Final diagnosis	Pre-morbid, at discharge on admission, 24 h after the admission to hospital NCCT, CTA, CTP during 24–36 h after the admission in indicated patients stroke, stroke mimics
Follow-up visit	
mRS value Recurrence of symptoms Clinical condition	

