### Determination of the definitive diagnosis

Two neurologists specialised in treating and diagnosing stroke will confirm the diagnosis independently.

The following patients will be diagnosed with an ischaemic stroke:Patients with a finding of hypodensity corresponding with subacute ischaemia on the initial brain CT examination.Patients with a new subacute ischaemic lesion on the follow-up NCCT scan within 36 h from the onset of the neurological deficit.Patients with an ischaemic brain lesion on their MRI scan within 3–7 days from the onset of the neurological deficit.

The diagnosis of SM will be determined by the following parameters:organic lesion of aetiology other than ischaemic stroke on the NCCT scan,negative CTP, discordant CTP, and negative control brain MRI,two neurologists and two radiologists specialised in treating and diagnosing stroke will confirm the diagnosis of SM independently, considering the correlation of imaging and clinical data (see clinical data checklist). The radiologists will also assess other thresholds during the CTP examination than the classically established ones (e.g., T max less than 6 s). Both stroke consultants will assess the final diagnosis for the whole group with and without knowledge of the CTP result.

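### The factor analysis tests imaging findings against a stroke/SM diagnosis that those same findings define, so their associations are inflated by construction and cannot be read as factors

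*Protocol article*

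**What the plan says.** The Statistic analysis section of the protocol article gives the aim as follows: "The analysis involves appropriate statistical tests and logistic regression to assess factors influencing clinical diagnosis". It names the candidate variables and the outcome: "The association between demographic, clinical, or radiographic variables and the clinical diagnosis (stroke and stroke mimic) is analysed using appropriate statistical tests". On the multivariable step it is tentative: "Eventually, logistic regression can be used for analysing the effect of multiple factors on the clinical diagnosis". It gives no covariate list, and it does not restrict the candidates to variables known at admission or to variables that play no part in the diagnosis.

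The section Determination of the definitive diagnosis lists three routes to ischaemic stroke:
- "Patients with a finding of hypodensity corresponding with subacute ischaemia on the initial brain CT examination"
- "Patients with a new subacute ischaemic lesion on the follow-up NCCT scan within 36 h from the onset of the neurological deficit"
- "Patients with an ischaemic brain lesion on their MRI scan within 3–7 days from the onset of the neurological deficit"

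For SM it lists a non-ischaemic organic lesion on NCCT, then "negative CTP, discordant CTP, and negative control brain MRI", with confirmation by two neurologists and two radiologists who weigh imaging together with clinical data. The Discussion repeats that the SM diagnosis combines clinical data with multimodal CT and MRI. The same section has both stroke consultants make the final diagnosis with and without the CTP result.

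Table 1 (Monitored parameters) places these items together under clinical data: "Type of treatment Multimodal brain CT scan on admission Follow-up NCCT Brain MRI results Final diagnosis". That block also holds NIHSS on admission and at 24 h, and mRS before the event and at discharge.

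**The concern.** A finding that puts a patient into the stroke group will be more frequent in the stroke group, whatever its real diagnostic value. A test of that finding against the diagnosis mostly measures how far the adjudicators relied on it. Calling it a factor that influences the diagnosis turns a rule of classification into an apparent result.

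There are two further risks. First, if such an image enters a logistic model it takes up nearly all the variation in the outcome. Age, history of epilepsy or migraine, blood pressure, glycaemia and admission NIHSS, which a clinician could use before imaging, are then estimated poorly or not at all. Second, *clinical* variables are not limited to admission. Treatment given, 24 h NIHSS and discharge mRS reflect the disease and the working diagnosis, so their association with the final diagnosis says nothing about what helps to recognise SM.

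The point concerns this factor analysis only. It is separate from the sensitivity and specificity tables.

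**Working it through.** The plan states no figure for the factor analysis. The minimum of 718 in the same section belongs to another comparison and does not enter here.

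**1. Variables against the diagnosis.**

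| Variable | Part in the stroke/SM diagnosis |
|---|---|
| Initial CT hypodensity | Stroke criterion |
| Follow-up NCCT lesion | Stroke criterion |
| MRI lesion / negative MRI | Stroke / SM criterion |
| Negative or discordant CTP | SM criterion; a CTP-unaware diagnosis is also made |
| CTA findings | Not a listed stroke criterion, though part of the multimodal CT considered for SM |
| Treatment, 24 h NIHSS, discharge mRS | Not criteria; they follow from the disease or working diagnosis |
| Age, sex, history, blood pressure, laboratory values, admission NIHSS | Not defined by any image |

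**2. Size of the inflation.** Take a marker that is positive in half the patients (assumption) and unrelated to true stroke. Let it decide the diagnosis in a share *w* of patients (assumption, shown as a range); elsewhere the diagnosis equals the truth, with 66% stroke as in the pilot project. Then

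P(stroke diagnosis | positive) = *w* + (1 − *w*) × 0.66

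P(stroke diagnosis | negative) = (1 − *w*) × 0.66

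- *w* = 0.10: 0.694 and 0.594, OR = (0.694/0.306)/(0.594/0.406) = 1.55
- *w* = 0.25: 0.745 and 0.495, OR = (0.745/0.255)/(0.495/0.505) = 2.98
- *w* = 0.50: 0.830 and 0.330, OR = (0.830/0.170)/(0.330/0.670) = 9.91

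Simulation with 3,000 patients and 200 runs agrees: median OR 1.6, 3.0 and 9.8, with the null rejected in every run. At *w* = 0 the OR is 1.00 with 3.5% rejections; at *w* = 1 it is infinite.

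**3. Separation.** Simulated cohorts of 3,000 with 34% SM, 60 runs per setting. NCCT sensitivity of 33% is from the Discussion. Assumed: 60% detection on follow-up NCCT, 90% on MRI, no false-positive lesions, CTP positive in 70% of strokes and 10% of SM.
- Age and a non-defining CTP marker only: no run separates.
- A defining image added, diagnosis follows the rule exactly: every run separates.
- Same, adjudicators depart from the rule in 1% of patients: 0–2% of runs.
- Same, 5% departure: none.

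**4. Masking without separation.** Pilot ages (71.1 and 67.9 years, SD 15.5), assumed seizure rates of 5% in stroke and 15% in SM, 60 runs per setting.
- No lesion variable: SE 0.0025 for age, 0.136 for seizure.
- Lesion variable with 3% disagreement: SE 0.0070 and 0.388, close to threefold.
- Lesion variable with 10% disagreement: age SE 0.0040, about 1.6 times.

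The pilot ages imply a log odds ratio per year of about (71.1 − 67.9)/15.5² = 0.0133. Divided by the SE this is 5.3 without the lesion variable and 1.9 with it at 3% disagreement. Age is accordingly significant in all runs without the lesion, and in about half with it (58% in one set of 60 runs, 47% in another). The age coefficient is not biased here; it loses precision.

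**5. Treatment as a factor.** If 40% of strokes and 8% of SM were thrombolysed (assumption), the crude OR is (0.40 × 0.92)/(0.60 × 0.08) = 7.7. If instead 18% of treated patients were SM (one reading of the trial figure in the Introduction), still with 40% of strokes treated, the share of SM treated is 0.66 × 0.40 × (18/82)/0.34 = 0.170 and the OR is (0.40/0.60)/(0.170/0.830) = 3.2. Either value describes a treatment decision.

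**The case against.** The strongest reply has four parts.

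**The regression is optional and has no covariate list.** No sentence enters a defining lesion into a model, and covariate choice is commonly left to the full protocol or SAP. This stands against any claim that the model *will* separate. A reader might infer that from the definition of stroke, but the diagnosis is adjudicated with clinical data, TIA is enrolled without appearing in the lesion criteria, and small departures from the rule almost remove separation. It does not answer the univariable tests: radiographic variables are named there as a choice, not left open.

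**Only some variables are affected.** A reader might infer that the whole factor analysis is circular. The documents do not support that. Demographic, history and laboratory variables are not defined by images, and CTA findings are not listed stroke criteria. This stands.

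**There is a safeguard for CTP.** The consultants also diagnose without the CTP result. This stands for CTP variables, but NCCT and MRI are not withheld, and the Statistic analysis section does not say which diagnosis is the outcome.

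**Table 1 is a data-collection list.** Its clinical block contains the final diagnosis itself, so it cannot be the predictor list, and describing treatment or discharge mRS by group is ordinary and serves the economic aim. This stands: that such items would be tested as factors is something the wording permits, not something it states. It is also tempting to say that the diagnosis precedes this care. The final diagnosis uses NCCT to 36 h and MRI at days 3–7, so acute treatment and 24 h NIHSS generally come before it. The objection to them as factors is that they are consequences of the disease or working diagnosis.

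**Conclusion.** The point holds for the defining images. The plan tests radiographic variables against a diagnosis built from initial CT hypodensity, follow-up NCCT lesions, MRI lesions and negative or discordant CTP, and describes the aim as finding factors. Those associations are inflated by construction.

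The size depends on how often an image decides the diagnosis, which the documents do not give. Over an assumed range of 10% to 50%, an uninformative marker would show an OR from about 1.6 to 9.8, always significant at 3,000 patients. Masking of admission predictors is conditional on a defining image entering the optional model, and separation needs in addition a diagnosis that follows the imaging rule without exception. Admission associations are not circular in this way, although adjudicators do see clinical data. The simulated standard errors and the treatment odds ratios are illustrations under assumed inputs, not results from the documents.

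The analysis is secondary, but the wording should be changed because it alters what can be concluded.

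**What to change.** Amend the Statistic analysis section as follows:
- Restrict the association tests and the logistic regression to admission variables outside the reference standard: age, sex, comorbidities, medication, blood pressure, laboratory values, admission NIHSS and type of deficit.
- Report the defining images (initial NCCT hypodensity, follow-up NCCT, MRI) and post-admission variables (treatment type, 24 h NIHSS, discharge mRS) by diagnosis, descriptively, without p-values and not as factors.
- Evaluate CTP variables only against the consultants' diagnosis made without knowledge of the CTP result.
- State which version of the diagnosis is the outcome of each analysis.

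A ban on testing any imaging variable would go further than needed, since it would also remove CTA and CTP variables that the study sets out to examine.

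The cost is a few sentences of analysis wording and fewer p-values. Data collection is unchanged, because both versions of the diagnosis are already planned.

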### Stroke protocol

#### Multimodal CT

All patients with acute neurological deficits (stroke, transient ischaemic stroke (TIA), or SM) will undergo neuroimaging diagnostic procedures as per the stroke protocol, i.e., initial multimodal brain CT (NCCT, CTP, and computed tomography angiography (CTA)), followed by follow-up NCCT within 24–36 h.

The basic CTP parameters define perfusion maps, which express the mean transit time, cerebral blood flow, and cerebral blood volume. Currently, the maps defining the so-called maximum time (Tmax) are also essential. The AI software package allows us to determine the extent of irreversible ischaemia (decrease in CBF below 30% of the reference bilateral value) and potentially the tissue that can be rescued, i.e., penumbra (prolongation of Tmax over 6 s).

Type of CT device—CT Force Siemens.

Stroke protocol: Unenhanced brain: 120 kV (CarekV), 300 mAs (CareDose), collimation 128 × 0.6 mm rotation time 0.5 s Recon: slice 0.75 mm, 5 mm, kernel Hr 40.

CTP: 70 kV, 200 mAs, collimation 48×1.2 mm, brain coverage-4D range: 114 mm.

Cycle time 1.5 s exam time 45 s rotation time 0.25 s contrast medium—40 mL intravenous.

CTA: 120 kV (CarekV), 84 mAs (Care Dose), collimation 128 × 0.6 mm.

Recon: slice 0.5 mm, 3 mm, kernel Hr 36, contrast medium—50 mL intravenous.

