#### MRI examination

All patients without a confirmed concordant hypoperfusion or cerebral ischaemia on their previous CT scans will undergo an MRI examination between the third and seventh day after admission to hospital to confirm the diagnosis of SM.

The MRI examination will be performed using the Siemens Prisma, 3.0 T scanner (Siemens, Erlangen, Germany). The imaging protocol includes:localisers;diffusion weighted imaging (DWI) with b-factor values 0, 400, and 800 s/mm2, calculated b-value of 1,000 s/mm2. ST 3.0 mm, GAP 0.6 mm, TR 2900 ms, TE 60 ms, FOV 256 mm, BW 868 Hz/Px, number of slices 40, TA 2:09;reconstructed maps of an apparent diffusion coefficient (ADC maps);3D FLAIR sequence. The examination will be performed in the sagittal plane with 1 mm MPR axial and coronal reconstructions. TR 5500 ms, TE 383 ms, ST 1 mm, number of slices 160, GAP 0, TI 1800 ms, FA T2 Var. deg., BW 751 Hz/Px, TF 220, TA—acquisition time 3:46. Total examination time 6:12+ shimming time.

Follow-up brain MRI will be performed on the following patients as per the stroke protocol:Patients with a negative initial multimodal CT scan.Patients with discordant CTP results, which means that the location of the hypoperfusion does not correspond with the neurological symptoms, or patients with CTP technical artefacts.Patients with a negative follow-up brain NCCT.Patients with an NIHSS score of zero upon admission to the hospital and 24 h after the onset of TIA.

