## Discussion

This project aims to clarify stroke and SM symptoms in hospital care, potentially modifying care provision. It could substantiate international publications and validate the role of multimodal CT in stroke and SM diagnosis.

It is common knowledge that the examination with the highest sensitivity and specificity for the diagnosis of ischaemic stroke is the MR examination of the brain (16). MR examination has numerous contraindications, and as part of an acute diagnosis, stroke is not routinely used. On the other hand, multimodal CT examinations (including non-contrast head CT (NCCT), head and neck CT angiography (CTA), and CTP) may play a significant role in providing accurate information about brain pathology in a short period of time. NCCT (17) and head and neck CTA, which are commonly used for the detection of large vessel occlusion, remain the gold standard in neuroimaging diagnostics in the case of suspected stroke, whilst CTP may play an important role in the diagnosis of SM. However, CTP is currently not a standard part of the diagnostic procedure in most stroke centres. Most patients with SM exhibited discordant clinical findings when compared to CTP imaging. Normal or entirely discordant Tmax of 6 s abnormalities are more common in patients with SM. Therefore, CTP could be crucial when deciding on the use of intravenous thrombolytic therapy (4). The sensitivity of acute NCCT examination for the diagnosis of ischaemic stroke is low (33%) (5).

The outcome of this project is based on the evaluation that the combination of NCCT, CTA, and CTP is superior to NCCT alone or the combination of NCCT and CTA in the diagnosis of SM in patients with acute neurological deficits. The final diagnosis of SM will be determined based on a unique combination of knowledge of clinical data and multimodal CT and MRI results.

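### The available-data rule permits failed CT perfusion scans to leave only the accuracy table that includes perfusion, so the CT combinations can be compared in different patients and the triple combination can look better than it is

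*Protocol article*

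**What the plan says.** Four places in the protocol article bear on this.

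- **Statistic analysis.** The accuracy measures are listed as "including accuracy, sensitivity, specificity, positive predictive value, and negative predictive value", with confidence intervals. The same paragraph ends by saying that "statistical analyses will be performed using appropriate statistical software (R, STATA) with maximum available data". It gives no rule for a scan that was done but cannot be read.
- **Multimodal CT.** Every patient is to have "initial multimodal brain CT (NCCT, CTP, and computed tomography angiography (CTA)), followed by follow-up NCCT within 24–36 h". All three CT components are therefore planned in each patient, and the comparison of combinations is paired by design.
- **MRI examination.** One group sent to follow-up MRI is those in whom "the location of the hypoperfusion does not correspond with the neurological symptoms, or patients with CTP technical artefacts". Failed CTP scans are thus foreseen, and a reference examination is planned for these patients.
- **Discussion.** The project rests on showing that "the combination of NCCT, CTA, and CTP is superior to NCCT alone or the combination of NCCT and CTA" for diagnosing stroke mimics.

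The section on the definitive diagnosis names "negative CTP, discordant CTP, and negative control brain MRI" among the parameters for a stroke mimic. It does not place a technically failed CTP.

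**The concern.** A patient whose CTP is spoiled by artefact has readable NCCT and CTA and, through MRI, a final diagnosis. What is missing is a usable index test. That is a different problem from missing verification by the reference standard.

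Under an available-data rule taken at its word, this patient counts in the NCCT and NCCT+CTA tables and drops out of the table that needs CTP. Two things follow:

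- The paired design is lost. The difference between combinations mixes a difference between tests with a difference between patient sets.
- The triple combination is judged only where CTP worked. The stated aim is a diagnostic procedure for consecutive patients with suspected stroke, and for them an unreadable scan is part of how the test performs.

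**Working it through.** **The plan's own figure.** The only related number is the sample size: "A minimum of 718 patients is required to demonstrate significant differences between diagnostic approaches". For 0.34 against 0.24, two-sided 5%, 80% power:

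n per group = [1.960 × √(2 × 0.29 × 0.71) + 0.842 × √(0.34 × 0.66 + 0.24 × 0.76)]² / 0.10² = 323 after rounding up, so 646 in total.

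646 / 0.90 = 718 after rounding up. The figure is matched only with a 10% allowance that the article does not state. It says nothing about how failed scans are counted. Its 0.34 is the pilot's proportion of stroke mimics, so its 10-point effect is not a like-for-like yardstick for diagnostic accuracy.

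**Inputs for the size.** From the article: 3,000 planned patients and 34% stroke mimics in the pilot. The article gives neither a CTP failure rate nor an accuracy, so the following are assumptions: failure rate f = 5% to 10%; 85% correct for the triple combination when CTP is readable; 60% correct for NCCT+CTA, taken as the same in patients with failed CTP.

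**Step 1, patients affected.** 3,000 × 0.05 = 150; 3,000 × 0.10 = 300.

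**Step 2, overall proportion correct under three rules.**

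| Rule for failed CTP | Formula | f = 5% | f = 10% | Available-data figure is higher by |
|---|---|---|---|---|
| Dropped (available data) | 0.85 | 85.0% | 85.0% | – |
| NCCT+CTA carried forward | (1−f) × 0.85 + f × 0.60 | 83.75% | 82.5% | 1.25 to 2.5 points |
| Counted as incorrect | (1−f) × 0.85 | 80.75% | 76.5% | 4.25 to 8.5 points |

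**Step 3, effect on the comparison.** The apparent gain over NCCT+CTA is 85 − 60 = 25 points with available data. It is 23.75 to 22.5 points with carry-forward, and 20.75 to 16.5 points with failures counted as incorrect.

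**Step 4, wider assumptions.** With failure from 2% to 15% and 80% to 90% correct when readable, counting failures as incorrect lowers the figure by between 0.80 × 0.02 = 1.6 points and 0.90 × 0.15 = 13.5 points. At the other extreme, if every failure were counted as correct, 80% would rise to 80.4% (f = 2%) or 83.0% (f = 15%).

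**Step 5, direction by measure.** Assume stroke sensitivity 0.80 and specificity 0.90 in readable scans, f = 10%, and failures counted as negative for stroke.

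- Sensitivity: 0.90 × 0.80 = 0.72, so dropping failures overstates it by 8 points.
- Specificity: 0.90 × 0.90 + 0.10 = 0.91, so dropping failures understates it by 1 point.
- Overall accuracy at 34% mimics: 0.66 × 0.80 + 0.34 × 0.90 = 83.4% with failures dropped, against 0.66 × 0.72 + 0.34 × 0.91 = 78.5% with them kept.

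**Step 6, unequal patient sets alone.** Suppose NCCT+CTA has sensitivity 0.60 where CTP is readable and 0.40 to 0.80 where it failed. At f = 10%, all patients together give 0.90 × 0.60 + 0.10 × 0.40 = 0.58 up to 0.90 × 0.60 + 0.10 × 0.80 = 0.62. The comparator moves by up to 2 points either way only because the patients differ.

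**The case against.** The strongest reply is that the article nowhere says failed scans are excluded. The available-data clause is general, closes a sentence on significance level and software, and does not mention CTP. An artefact scan is a test that was done, and the patient still has NCCT and CTA, so using all available data could mean using those readings. The MRI section also lists artefacts in the same item as discordant CTP; if they are analysed that way, nobody drops out. Finally, the handling of indeterminate results often sits in an analysis plan, which is not shown, and the STARD diagram is not shown either.

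Much of this stands. Exclusion is permitted, not stated, and an unseen document may settle it. Two parts carry less weight. The MRI section sets "patients with CTP technical artefacts" apart from discordance by an alternative, so what the two groups clearly share is the route to MRI. If unreadable scans were counted as discordant, they would count towards a stroke mimic, and that too would need saying. The article also does more than stay silent: it states an available-data rule in the paragraph on accuracy, and a different rule elsewhere would have to be reconciled with it.

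A reader might also infer that CTP is the only component that can fail. The article names only CTP artefacts; it does not say that NCCT and CTA are always readable.

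**Conclusion.** The point holds as a weakness in the stated rule. Read literally, it permits patients with failed CTP to leave only the table that includes CTP. The comparison behind the superiority statement can then rest on different patients and can overstate the overall accuracy and stroke sensitivity of the triple combination.

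The size rests wholly on assumed rates. At 5-10% failure, 85% correct when readable and 60% for NCCT+CTA, it is 1.3 to 2.5 points against carry-forward and 4.3 to 8.5 points against counting failures as incorrect. On these inputs the advantage of adding CTP shrinks but does not vanish.

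A reader might infer that failed scans will be dropped and that CTP accuracy will be inflated on every measure. The article supports neither. No exclusion is stated, and dropping failures can slightly understate specificity for stroke, which is sensitivity for stroke mimics.

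**What to change.** In the statistical analysis section, replace the general clause, for the comparison of combinations, with these rules:

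1. Compare NCCT, NCCT+CTA and NCCT+CTA+CTP in one common set: all enrolled patients with a final diagnosis.
2. When CTP is non-diagnostic, take the NCCT+CTA reading as the result of the triple combination. This is a rule for analysis only and changes nothing in patient care.
3. Report the number of non-diagnostic CTP scans.
4. Give two sensitivity analyses: failures counted as incorrect, and the available-data analysis as now worded.

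If the full protocol or analysis plan already holds such rules, align the published sentence with them. No new data are needed. The cost is a change of wording, a little programming, and a reported CTP accuracy that is likely to be slightly less favourable. Settling the rule before results are seen also removes a choice that could otherwise be made in CTP's favour.

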**Methodology:**

In this study, we will include 3,000 patients consecutively admitted to the comprehensive stroke centres with a diagnosis of suspected stroke. On the basis of clinical parameters and the results of multimodal CT and magnetic resonance imaging (MRI), the diagnosis of stroke and SM will be established. To clarify the significance of the use of the multimodal CT scan, the analysis will include a comparison of the blinded results for each imaging scan performed by radiologists and AI technology and a comparison of the initial and final diagnosis of the enrolled patients. Based on our results, we will compare the economic indicators and costs that would be saved by not providing inadequate treatment to patients with SM.

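### The economic dominance test is one-sided: it prices neither CT perfusion nor strokes labelled as mimics, so withholding thrombolysis can never come out badly

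*Protocol article*

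**What the plan says.** The Protocol article describes the economic evaluation mainly under Statistic analysis. Two sentences there fix how it works:

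- Cost: "The calculation of costs is based on the average cost of thrombolysis and its associated treatment, representing the incremental cost (IC").
- Decision rule: the evaluation is organised as a "test of dominance of improved results (meaning fewer complications associated with the administration of thrombolysis) and lower costs".

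The Abstract (Methodology) gives the direction of the comparison: "we will compare the economic indicators and costs that would be saved by not providing inadequate treatment to patients with SM".

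The same economic text also states a wider scope. The health technology assessment is described as "analysing not only the QoL of patients but also the costs associated with the treatment of stroke and SM", and "The results will be reported as expected ICs and effects (E) expressed in quality-adjusted years of life (QALY"). The section on quality of life and pharmacoeconomic analysis adds that "the mRS provides a quantifiable outcome measure that can be related to QALYs and other economic evaluations".

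Three other statements matter. The Discussion says that most stroke centres do not have CTP in their standard work-up, and that it could be decisive for giving intravenous thrombolysis. The Introduction calls thrombolysis the first-choice treatment in stroke.

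**The concern.** The innovation being valued is the addition of CTP to non-contrast CT and CT angiography. On the article's own account CTP is an extra test in most centres, so its cost belongs in the increment. The stated incremental cost does not contain it.

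On the article's own account, too, CTP may change who is thrombolysed. It can then err in two ways: an SM patient is still treated, or a true stroke is read as SM and loses first-choice treatment. The definition of improved results sees the first error and not the second. A stroke left untreated because of a false SM reading has no thrombolysis cost and no thrombolysis complication, so the test scores it as a gain or, at worst, as nothing.

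The Discussion and Conclusion look ahead to changing care provision and reducing costs. A test that cannot show that withholding treatment caused net cost or harm cannot carry that argument.

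**Working it through.** **No plan figure to reproduce.** The article gives no unit cost, thrombolysis rate, complication rate or QALY weight. That is not the complaint, since a condensed article may leave these to a fuller plan. The check is how the stated definitions behave.

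**Inputs**
- SM share 34% (37 of 109, pilot project). Per 1,000 suspected strokes: 340 SM and 660 strokes.
- *t* = share who would be thrombolysed without CTP. Assumed 20%, range 10–30%, and equal in SM and stroke.
- *q* = share of those would-be-treated SM in whom treatment is withheld (assumed).
- *f* = share of those would-be-treated strokes in whom it is withheld (assumed).
- CTP is taken only to withhold treatment, the direction described in the Abstract.

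**Formulas**
- Treatments avoided = *q* × 340 × *t* + *f* × 660 × *t*.
- Incremental cost on the stated definition = −(treatments avoided) × cost of one thrombolysis.

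**Results at *t* = 20%** (68 SM and 132 strokes would be treated)

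| Rule | *q* | *f* | Avoided in SM | Avoided in strokes | Total |
|---|---|---|---|---|---|
| Good | 0.90 | 0.05 | 61.2 | 6.6 | 67.8 |
| Chance | 0.50 | 0.50 | 34.0 | 66.0 | 100.0 |
| Mostly wrong | 0.10 | 0.90 | 6.8 | 118.8 | 125.6 |
| No decision changed | 0 | 0 | 0 | 0 | 0 |

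**Two readings of what counts as a saving**
- Every withheld treatment counts: savings rank 125.6 > 100 > 67.8, so the worst rule looks best on cost and on complications.
- Only treatment withheld in SM counts, as the Abstract suggests: savings are 61.2, 34.0 and 6.8. Size now follows recognition of SM, but the 6.6, 66 or 118.8 untreated strokes still carry no penalty.

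On both readings the incremental cost is zero or negative.

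**With CTP priced.** CTP saves money only if its cost per patient is below (treatments avoided ÷ 1,000) × cost of one thrombolysis. For the good rule:

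| *t* | All withheld | SM only |
|---|---|---|
| 10% | 33.9/1,000 = 3.4% | 30.6/1,000 = 3.1% |
| 20% | 67.8/1,000 = 6.8% | 61.2/1,000 = 6.1% |
| 30% | 101.7/1,000 = 10.2% | 91.8/1,000 = 9.2% |

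The stated test cannot detect that this condition fails.

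**With missed strokes valued.** Net QALYs are positive only if the mean loss per stroke left untreated is smaller than (SM spared ÷ strokes untreated) times the mean gain per SM spared. That ratio is 61.2/6.6 = 9.3 for the good rule and 34/66 = 0.52 for the chance rule. With equal *t* in both groups, *t* cancels. The accuracy of CTP therefore decides the sign of the effect, and the dominance criterion has no term through which it could.

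**The case against.** The strongest reply is that the section is wider than its two narrow sentences. It names the costs of treating both stroke and SM and reports effects in QALYs, and mRS is linked to QALYs. A QALY effect over all patients could capture the loss in missed strokes. Saying that cost is based on thrombolysis is also not the same as saying that it consists of nothing else, and CTP unit costs or model structure may sit in a plan not shown.

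This has weight against three stronger readings that a reader might infer:

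- *The evaluation counts only thrombolysis costs and complications.* Not supported: the QALY and treatment-cost statements stand in the same section.
- *CTP dominates whatever its accuracy.* Not supported: if only treatment avoided in SM counts, the saving falls from 61.2 to 6.8 per 1,000 as recognition of SM worsens.
- *A favourable result is guaranteed.* Not supported: if no thrombolysis decision changes, the saving is zero and there is no dominance.

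Nor should all MRI be charged to CTP. Under MRI examination, the scan at days 3–7 serves to confirm SM, so it is largely study verification.

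The reply does not remove the core. The section goes on from its wide scope to state how costs are calculated and what improved results means, and both statements are narrower than that scope. Including CTP cost or missed strokes would mean rewriting those definitions, not adding detail beneath them.

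**Conclusion.** The point holds in this form: the dominance test as worded is one-sided, and it conflicts with the broader QALY and treatment-cost scope of the same section. On its definitions, withholding thrombolysis is scored as favourable or neutral and never as net cost or harm.

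The conclusion about direction rests on the article's wording alone. The sizes (67.8 against 100 treatments avoided; break-even near 6.8% or 6.1% of one thrombolysis) rest on the pilot's 34% SM and on assumed values of *t*, *q* and *f*. They illustrate how the test behaves and do not predict the trial's result. The diagnostic accuracy aim is unaffected; what is at risk is the economic claim built on it.

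**What to change.** Replace the two narrow definitions so that they match the stated QALY scope:

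1. **Incremental cost** = cost of CTP in all suspected strokes, with its software and any further imaging it would trigger in routine care, minus thrombolysis and complication costs avoided in SM, plus costs of strokes labelled SM.
2. **Incremental effect** = net QALYs over both error types (SM treated, stroke labelled SM), relative to non-contrast CT alone or with CT angiography.
3. **Accuracy inputs** = the study's own sensitivity and specificity, for CTP and for the comparator, with their uncertainty carried through by probabilistic sensitivity analysis.
4. **Reporting** = incremental cost and incremental QALYs with uncertainty, with dominance as one possible result and not the organising test.

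The cost is extra modelling and the collection of unit costs. It needs no more patients and no change to the imaging pathway. The result may be less favourable to CTP.
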